**The Victorian Emergency Minimum Dataset (VEMD)** is a state-wide emergency dataset collected for all presentations to public emergency departments and maintained by the Victorian Government's Department of Health and Human Services. Currently, VEMD data, which is collected by ED staff (including clerical and health professionals), includes demographic (e.g. age, sex, usual place of residence), administrative (e.g. triage code, destination from ED) and clinical data (e.g. primary diagnosis). This dataset is used for epidemiological purposes, health services planning and coordination; policy assessment and formulation; and clinical research and quality improvement.

**The Victorian Admitted Episodes Dataset (VAED)** comprises demographic, clinical and administrative details for admitted episodes of care occurring in Victorian hospitals, rehabilitation centres, extended care facilities and day procedure centres. VAED data is used to provide equitable funding to public hospitals under the casemix system, support health services planning, policy formulation and epidemiological research, and meet national data reporting requirements.

**The Victorian Cardiac Arrest Registry (VACAR)** records details of all OHCA events where EMSs are in attendance. In-field treatment data are captured electronically using computer tablets operated by paramedics. A highly sensitive search filter is used to identify potential cardiac arrest cases from a database of electronic patient care records. Potentially eligible cases undergo manual review by registry personnel, and cases meeting eligibility criteria are entered into the registry extracting over 150 data points including the Utstein-style descriptors. Complete case ascertainment is assured through the review of computer-aided dispatch records, emergency call logs, and paper-based treatment records. Paramedics are also required to report cardiac arrest cases and submit electrocardiogram recordings.

**The Victorian Ambulance STEMI Quality Initiative (VASQI)** is a clinical quality registry that aims to facilitate quality improvement by collecting and monitoring data regarding the treatment and outcome of paramedic suspected STEMI cases. The VASQI incorporates both

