## 2.5 Outcomes

Outcomes will be examined for adult (aged 18 years or older) residents of the eight LGAs. All outcomes, except survey data, were collected continuously between December 1st 2022 to March 31st 2023 for the main trial and to March 31st 2024 for long-term follow-up. The survey data was collected at three-time points; December 2021-January 2022 (control), August 2022-September 2022 (half-way), April-May 2023 (completion). This Statistical Analysis Plan provides plans for the analysis of the main trial; the analysis of long-term follow-up data will be covered in a subsequent document.

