The following will be obtained from the Victorian Department of Health's Victorian Admitted Episodes Dataset (VAED):

- Rates of ACS survival (the proportion of ACS patients surviving to hospital discharge to be compared between groups)

The following will be obtained from the Victorian Cardiac Arrest Registry (VACAR):

- Numbers of patients with an out-of-hospital cardiac arrest by LGA and month. Adult population sizes of LGAs will be obtained from the Australian Bureau of Statistics to convert this to a rate for each LGA in each month.[11]
- Survival to hospital discharge following an out-of-hospital cardiac arrest (proportion of patients with out-of-hospital cardiac arrest surviving to hospital discharge out of all patients with out-of-hospital cardiac arrest to be compared between groups[11])

The following will be collected from the Ambulance Victoria computer-aided dispatch (CAD) records:

- Calls to EMS for chest pain (the proportions of chest pain [event type 10] calls to EMS out of all calls to EMS to be compared between groups [12])
- Calls to EMS for non-chest pain (the rate of non-chest pain [non-event type 10] calls to EMS to be compared between groups; adult population sizes of LGAs will be obtained from the Australian Bureau of Statistics to convert this to a rate for each LGA in each month).

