### **3.8.2 Binary outcomes: whether patient delay time $\leq 60$ mins (in STEMI and suspected STEMI patients); whether prehospital delay time $\leq 120$ mins (in STEMI, ACS, and suspected STEMI patients); survival to hospital discharge (in ACS patients); survival to hospital discharge following an out-of-hospital cardiac arrest; acute coronary syndrome emergency department presentations via General Practitioners; calls to EMS for chest pain.**

These binary outcomes will be analysed according to the approach outlined in Section on 3.7.1. Analysis of the survival to hospital discharge following an out-of-hospital cardiac arrest outcome will only include participants who had an out-of-hospital cardiac arrest.

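### The SAP states no cause restriction for OHCA incidence or survival, so arrests of non-cardiac cause would dilute the incidence effect toward the null

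*Supplement*

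**What the plan says.** Both OHCA outcomes come from the Victorian Cardiac Arrest Registry (VACAR).

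- **Incidence** (SAP 2.5.2) is "Numbers of patients with an out-of-hospital cardiac arrest by LGA and month", turned into a rate with the adult population of each LGA. SAP 3.8.4 analyses it with a marginal Poisson model.
- **Survival** (SAP 2.5.2) is the "proportion of patients with out-of-hospital cardiac arrest surviving to hospital discharge out of all patients with out-of-hospital cardiac arrest". SAP 3.8.2 sends it to the methods of 3.7.1 and adds only that the analysis "will only include participants who had an out-of-hospital cardiac arrest".
- **Source.** The amended protocol, under data collection and data sources, says that VACAR "records details of all OHCA events where EMSs are in attendance".

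Three things qualify this. SAP 2.5 says: "Outcomes will be examined for adult (aged 18 years or older) residents of the eight LGAs". The protocol says that "cases meeting eligibility criteria are entered into the registry", without listing the criteria. Both OHCA outcomes in SAP 2.5.2 also cite an evaluation of a public awareness campaign's effect on OHCA incidence and mortality.

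No analysis by cause is planned. The sensitivity and subgroup analyses in SAP 3.7.2 to 3.7.4 sit under the primary outcome. The protocol does extend subgroup analyses to secondary outcomes, but its examples are age, sex and country of birth. The SAP's Table 5 shell has one row for OHCA incidence and one block for OHCA survival.

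**The concern.** The education covers risk factors for acute coronary syndrome (ACS), its symptoms and calling an ambulance. It could plausibly change how many arrests follow an untreated coronary event. It has no evident route to arrests from trauma, drowning or overdose. If such arrests are in the count, they add events that the intervention leaves alone, and the estimated rate ratio moves toward 1.

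Elsewhere the SAP ties outcomes to the target condition in its own text. ED presentations are counted by a final ED diagnosis of ACS, and chest-pain calls by the dispatch event type. The OHCA outcomes have no such tie.

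Reducing OHCA incidence and improving OHCA survival are both secondary objectives in the protocol. OHCA incidence is also named as an input to the cost-consequences analysis. A diluted null result could be read there as evidence that the campaign does not affect cardiac arrest.

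**Working it through.** **The plan's own figure.** There is none for these outcomes. The sample-size section (SAP 2.8) covers ambulance arrival and a survey outcome. The documents give no OHCA count, cause mix, survival proportion or target effect. Everything below illustrates a mechanism on assumed values.

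**Step 1: dilution of incidence.** Let *s* be the share of control-period arrests that are cardiac, and let the intervention act only on those, with rate ratio RR. Then

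observed RR = *s* × RR + (1 − *s*).

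| Assumed *s* | True RR 0.80 | True RR 0.90 |
|---|---|---|
| 0.8 | 0.64 + 0.20 = 0.84 | 0.72 + 0.20 = 0.92 |
| 0.7 | 0.56 + 0.30 = 0.86 | 0.63 + 0.30 = 0.93 |
| 0.6 | 0.48 + 0.40 = 0.88 | 0.54 + 0.40 = 0.94 |

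**Step 2: do the extra events pay for the dilution?** Take equal person-time, Poisson counts and no clustering, with *C* cardiac arrests under control.

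- Cardiac arrests only, RR 0.80: variance of the log ratio = (1 + 1/0.80)/*C* = 2.25/*C*, so z = 0.2231/√2.25 × √*C* = 0.149√*C*.
- All arrests, *s* = 0.8: variance = 0.8 × (1 + 1/0.84)/*C* = 1.752/*C*, so z = 0.1744/√1.752 × √*C* = 0.132√*C*.
- All arrests, *s* = 0.6: variance = 0.6 × (1 + 1/0.88)/*C* = 1.282/*C*, so z = 0.1278/√1.282 × √*C* = 0.113√*C*.

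The z statistic falls to 0.89 and 0.76 of its cardiac-only value. A cardiac-only comparison with 80% power (expected z = 1.96 + 0.84 = 2.80) would have about 70% and 57% power, since 0.885 × 2.80 − 1.96 = 0.52 and 0.759 × 2.80 − 1.96 = 0.17. In this simple setting, narrowing the population loses events but gains power.

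**Step 3: survival and cause.** If a survival gain is confined to cardiac arrests and the cause mix is the same in both conditions, the all-arrest risk difference is *s* times the cardiac one.

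**Step 4: survival and attempted resuscitation.** Assume survival of 10% versus 15% when resuscitation is attempted and none otherwise.

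| Share attempted | Risk difference (points) | Odds ratio |
|---|---|---|
| 100% | 5.0 | 1.59 |
| 60% | 3.0 | 1.55 |
| 50% | 2.5 | 1.54 |
| 40% | 2.0 | 1.53 |

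The risk difference shrinks in proportion, but the odds ratio hardly moves. Little precision is lost either. With individual randomisation, 80% power and no clustering, 10% versus 15% needs 686 attempted cases per arm. At a 60% share, the all-arrest comparison needs 1,209 patients per arm, of whom 0.60 × 1,209 ≈ 725 are attempted cases. Mixing in untreated arrests is therefore a much weaker argument than mixing in unrelated causes.

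**The case against.** **The definition may exist outside these documents.** The cited campaign evaluation may hold an OHCA case definition, and VACAR applies its own eligibility criteria. This stands as a limit on what can be claimed. A reader might infer that every EMS-attended arrest will be counted. The documents support only that no cause restriction is stated. It does not remove the need to state one: ACS presentations also carry a citation, and the SAP still gives their criterion in the text.

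**The outcome matches the objective as worded.** The protocol's objectives speak of OHCA incidence and survival without naming a cause. This is fair, and it is a reason to keep the all-arrest analysis. It does not make that analysis the more informative one for this intervention.

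**Arrests without attempted resuscitation.** A reader might infer that these too are arrests the education cannot affect, and that survival should be confined to treated patients. The documents point the other way. The protocol's background says that most ACS deaths happen in the community, usually before the emergency system is activated and after hours of symptoms. Untreated arrests plausibly include deaths the campaign aims to prevent. Whether resuscitation is attempted may also depend on how early someone calls, so restricting on it would condition on something the intervention can change. The objection stands against using that restriction for the main analysis.

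**Model failure.** Low survival could strain the identity-link binomial model, but SAP 3.7.1 also reports a marginal odds ratio and relies on it alone if the identity-link model does not converge.

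**Flooding.** A reader might suppose that the October to November 2022 floods added non-cardiac arrests unevenly. No passage links the floods to arrests. SAP 3.4 says that all trial LGAs were affected, to varying degrees, and the period terms absorb whatever was common. An uneven excess is possible but not shown.

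**Conclusion.** The point holds for cause. The current SAP and protocol state no cause restriction for either OHCA outcome and plan no analysis by cause. Followed as written, they would mix in arrests that heart-attack education cannot plausibly affect, and this would bias the incidence effect toward the null.

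The size cannot be derived from the documents. The range of 0.84 to 0.88 for a true rate ratio of 0.80 rests on an assumed cardiac share of 80% to 60% and on no effect in other arrests. The power figures further assume Poisson counts, equal person-time and no clustering. They show direction and are not a forecast for this trial.

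The point does not extend to making attempted resuscitation the main survival denominator. It also does not touch the trial's main conclusion: these are secondary outcomes with no stated power, and the primary outcome comes from a different dataset. It is an inexpensive improvement worth making.

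**What to change.** In SAP 2.5.2, 3.8.2 and 3.8.4:

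1. State the OHCA case definition in the text, covering cause and resuscitation status, including any definition now carried by the citation or by the registry's eligibility criteria.
2. Analyse OHCA incidence and survival in adult residents with an arrest of presumed cardiac cause.
3. Keep the all-arrest versions of both outcomes as supportive results.
4. Report survival among attempted resuscitations as supportive only, and say why.

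Add matching rows to the Table 5 shell.

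The protocol describes the registry as "extracting over 150 data points including the Utstein-style descriptors", so fields for cause and resuscitation status should exist. It does not say that they are in the trial's de-identified extract, and incidence is described as counts by LGA and month. Confirm this with the data custodian first; if they are absent, a further data request is needed.

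Otherwise the cost is SAP wording and a few more table rows. The statistical price is fewer events and a cause that is presumed rather than proven. Some misclassification will remain, and the supportive all-arrest results let readers judge its effect.

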### **Stepped wedge trial schematic**

The schematic for the Heart Matters stepped wedge trial is displayed below. It has 6 sequences, where 2 local government areas are assigned to each of the first and last sequences of the trial. Periods are each two months long, with transition periods between control and active implementation periods incorporated in each sequence.

Figure 1. Stepped wedge cluster trial design including baseline, transition, and active implementation periods.

[figure not shown]

LGA: Local Government Area

## 2.7 Research and statistical hypotheses

The primary research hypothesis is that the introduction of the Heart Matters education intervention will lead to an increase in the proportion of ACS patients arriving at the hospital via EMS.

The primary statistical hypotheses are as follows:

- **Null hypothesis:** no difference in the proportion of ACS patients that arrive at the emergency department via EMS will be the same before and after the introduction of the Heart Matters education intervention. That is, the risk difference is equal to 1.

- **Alternative hypothesis (2-sided):** The proportion of ACS patients arriving at the emergency department via EMS will not be the same before and after the introduction of the Heart Matters education intervention. That is, the risk difference is not equal to 1.

## 2.8 Sample size

The stepped wedge design in the schematic (a six-sequence stepped wedge design, with an implementation period and two clusters assigned to the first and last sequences) will give 80% power to detect a change in the proportion of ACS patients in the eight LGAs arriving via EMS by 11%[10, 12] from a baseline of 61% to 72%, with a two-sided significance level of 5%. This detectable difference depends on an average of 40 ACS patients admitted per LGA in each two-month period (i.e. a total of 2240 ACS patients) and on the intra-cluster correlation, estimated to be 0.09 using data from the Victorian Emergency Minimum Dataset (VEMD) (2011-2015). This data indicated that more complex correlation structures, with decaying correlations over time, were unnecessary. The Stepped Wedge Stata Program was used for the sample size calculation,[13] verified using the Shiny CRT app.[14] No adjustment was made for LGA or participant attrition, as health services routinely collect the outcomes.

A sample size calculation was also conducted for two online surveys to determine a change in the level of knowledge of ACS symptoms. An online survey in 2020,[7] showed 25% of adults in the intervention LGAs (20% state-wide) could not name any heart attack symptoms. To detect a change from 25% to 10%, with 80% power and 2-sided significance level, requires a survey of 72 adults in each LGA in months 1-2 and again in months 9-10, assuming an intracluster correlation of 0.1, and a cluster autocorrelation of 0.9.

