### *Study setting*

The study will be undertaken in eight LGAs in Victoria (3 in greater Melbourne and 5 in regional Victoria).

These LGAs were selected from the list of the 16 highest-risk Victorian LGAs (highest ranking for age-standardised rates of heart attacks) generated from the Victorian Heart Maps.

These LGAs were selected to meet the study's sample size requirements based on admission rates for ACS from the Victorian Emergency Medicine Dataset (VEMD). Estimates, from the 2013-2015 VEMD data, suggests 1,635 ACS events occur in these LGAs annually (annual range across LGAs=102 to 360).

*Table 1. Profiles of the 8 LGAs to be targeted (\*SED= Index of Relative Socio-economic Disadvantage).*

| LGA name | Area km2 | Residents | Index SED* | Median age | Males (%) | Born overseas (%) |
|----------|----------|-----------|------------|------------|-----------|-------------------|
| LGA1     | 489      | 207058    | 991        | 34         | 50        | 36%               |
| LGA2     | 503      | 207041    | 947        | 33         | 50        | 36%               |
| LGA3     | 31       | 86942     | 995        | 34         | 51        | 40%               |
| LGA4     | 2999     | 112267    | 981        | 38         | 49        | 8%                |
| LGA5     | 22082    | 54658     | 935        | 40         | 50        | 11%               |
| LGA6     | 432      | 40100     | 977        | 36         | 50        | 10%               |
| LGA7     | 4518     | 37595     | 967        | 45         | 50        | 7%                |
| LGA8     | 120.7    | 33655     | 986        | 40         | 50        | 8%                |

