### Sample size

The stepped wedge design in the schematic (a six-sequence stepped wedge design, with an implementation period and two clusters assigned to the first and last sequences) will give 80% power to detect a change in the proportion of ACS patients in the eight LGAs arriving via ambulance by 11%, from 61% to 72%, with a two-sided significance level of 5%. This detectable difference depends on the number of patients expected to be observed in each cluster (average of 40 patients per LGA in each two-month period; a total of 2240 patients) and on the intra-cluster correlation, estimated to be 0.09 using data from the VEMD (2011-2015). Examination of these aforementioned data indicated that more complex correlation structures, with decaying correlations over time, were not necessary. We used the Stepped Wedge Stata Program for the sample size calculation. No adjustment was made for LGA or participant attrition due to the outcomes being those routinely collected by health services.

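### The 40 ACS patients per LGA-period behind the stated 80% power do not match the protocol's only event rate (1,635 a year, or 34 per LGA-period); if that rate held, the analysed sample would be about 1,908 and power about 73-76%

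*Supplement*

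**What the plan says.** SAP section 2.8 describes "a six-sequence stepped wedge design, with an implementation period and two clusters assigned to the first and last sequences", with 80% power at the two-sided 5% level for a change in the proportion arriving by ambulance "from a baseline of 61% to 72" per cent. It makes this conditional on two inputs: "an average of 40 ACS patients admitted per LGA in each two-month period (i.e. a total of 2240 ACS patients", and "the intra-cluster correlation, estimated to be 0.09 using data from the Victorian Emergency Minimum Dataset (VEMD) (2011-2015". The latest protocol's Sample size section agrees ("average of 40 patients per LGA in each two-month period; a total of 2240 patients"), and its synopsis gives 2,240 as the sample size for the primary outcome.

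The same protocol's Study setting section says the LGAs were picked so that their ACS admission rates would provide the required sample. It then gives the rate: the 2013-2015 VEMD data "suggests 1,635 ACS events occur in these LGAs annually (annual range across LGAs=102 to 360". The SAP does not repeat this figure.

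SAP section 3.2 and the footnote to its proposed Table 1 exclude transition-period data from the analysis.

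**The concern.** The protocol offers 1,635 a year as the basis on which the LGAs can supply the sample, so it is not incidental background. It should therefore lead to the patient numbers in the power calculation, and it does not. The calculation needs about 17% more events a year than the protocol reports, and neither document says where the extra events come from. What is at stake is whether the stated power and detectable difference for the primary outcome follow from the plan's own evidence.

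**Working it through.** **Inputs**
- Eight LGAs and eight two-month periods (16 months): 64 LGA-periods. Source: protocol Table 4 and SAP section 2.6.
- One transition period per LGA, not analysed: 64 - 8 = 56 analysed cells. Launch periods are T2, T2, T3, T4, T5, T6, T7, T7. Source: protocol Table 4 and SAP Table 1.
- ICC 0.09, no decay over time, 61% against 72%, two-sided 5%. Source: SAP section 2.8.
- 1,635 ACS events a year in the eight LGAs. Source: protocol, Study setting.

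**Patient numbers**
- Stated: 56 x 40 = 2,240, which is exact.
- From the event rate: 1,635 / 8 LGAs / 6 periods a year = 34.06 per LGA-period.
- All 64 cells: 1,635 x 16/12 = 2,180, already below 2,240.
- Analysed cells: 2,180 x 56/64 = 1,907.5, a shortfall of 332.5 / 2,240 = 14.8%.
- Annual events needed for 40 per cell: 40 x 8 x 6 = 1,920, and 1,920 / 1,635 = 1.174.

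**Power method**

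The model for LGA-period means has fixed period effects, an intervention effect and a random LGA intercept. For each LGA's seven analysed cells, V = s2 x [((1 - 0.09)/m) I + 0.09 J]. Here s2 is the outcome variance, m the number of patients per cell, I the identity matrix and J a matrix of ones. The variance of the intervention effect is its diagonal element in the inverse of the sum over LGAs of X'V^-1X. Power = Phi(0.11/SE - 1.96), and the difference detectable with 80% power = (1.96 + 0.842) x SE.

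The documents do not state the convention for s2, so three are shown:
- at 61%: 0.61 x 0.39 = 0.2379
- pooled at 66.5%: 0.665 x 0.335 = 0.2228
- average of the two proportions: (0.2379 + 0.2016)/2 = 0.2198

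| Variance | m | SE | Power for 11 points | Detectable at 80% |
|---|---|---|---|---|
| At 61% | 40 | 0.0396 | 79.4% | 11.1 points |
| Pooled | 40 | 0.0383 | 81.9% | 10.7 points |
| Average | 40 | 0.0380 | 82.4% | 10.7 points |
| At 61% | 34.06 | 0.0428 | 73.0% | 12.0 points |
| Pooled | 34.06 | 0.0414 | 75.7% | 11.6 points |
| Average | 34.06 | 0.0411 | 76.3% | 11.5 points |

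Worked case: 0.11/0.0396 - 1.96 = 0.82, giving 79%; 0.11/0.0428 - 1.96 = 0.61, giving 73%.

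The plan's 80% therefore reproduces at 40 per cell with the transition cells dropped. Keeping those cells and counting them as intervention would give 92-94% at 40 per cell, so the stated figure does rest on the 56 analysed cells. The calculation is sound, and the discrepancy lies in the input of 40.

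**The case against.** The best defence is that nothing in section 2.8 is miscalculated. The product is exact, the power reproduces, and the SAP says openly that the detectable difference depends on 40 per LGA-period. The 1,635 is offered as an estimate from 2013-2015, while main-trial data collection ended in March 2023. Reaching 1,920 a year needs only about 2.0-2.3% growth a year over seven to eight years. The documents do not exclude that, so 40 may be the better figure. This stands. A reader might infer that the trial will analyse 1,908 patients, or that it is underpowered as a matter of fact. The documents support neither, only that the two figures are unreconciled.

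A second objection is that the loss is modest and depends on the variance convention. It is indeed only 4 to 7 percentage points below the stated 80%. Taking the variance at 72% alone brings 34.06 per cell up to 79.8%. But that convention gives 85.5% at 40 per cell, so it is not the one behind the stated 80%.

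A third is that version 1.1 of the SAP is dated March 2024, after main-trial collection closed, and that the results tables will show observed counts and confidence intervals. This also stands. It limits the consequence to how the planned sample size and power are described.

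**Conclusion.** The inconsistency holds. Both documents rest their power on 40 patients per LGA-period, while the only event rate stated, and the one said to have guided LGA selection, gives 34.06. Rounding or the treatment of transition cells cannot explain it, because even all 64 cells at that rate fall short of 2,240.

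Conditional on the 2013-2015 rate applying to the trial, the analysed sample is about 1,908 and power for 61% to 72% is about 73-76%. The chance of missing that effect is then 24-27% instead of 20%. This assumes an exchangeable ICC of 0.09, equal LGA sizes and a normal test.

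Two further inferences should not be drawn. Unequal LGA sizes could change the power, but the documents give only the range across LGAs, not the individual counts, so no single figure is justified. And neither document says that planned power will be used to interpret a null result; SAP section 3.1.2 commits to confidence intervals and p-values.

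**What to change.** In SAP section 2.8, the protocol's Sample size section and the synopsis, do one of the following:

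1. Restate the expected analysed sample as about 1,908, with 73-76% power for 11 points (or 80% power for 11.5-12 points), explicitly conditional on 1,635 events a year. Name the variance convention so that one value can replace the range.
2. Keep 40 and 2,240, cite the LGA counts or growth assumption that support them (about 1,920 events a year), and correct the 1,635 in the protocol's Study setting section.

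The second is preferable if newer counts exist. Either is a wording change with no effect on design, recruitment or analysis. The only cost of the first is a slightly less favourable stated power.
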